### Trial design and setting

This is a multi-centre, randomised controlled, double blinded trial comparing the clinical and cost-effectiveness of ketamine and morphine for severe pain following acute traumatic injury. It is a pragmatic, phase III trial working with two large NHS ambulance trusts with an internal pilot, aimed at mirroring existing practice of dealing with severe pain following acute traumatic injury. Participants will be followed up for 6 months. Adult patients (> = 16 years old) will be eligible for recruitment if they report severe pain following acute injury, in the pre-hospital environment and are determined by a paramedic to require parenteral morphine or equivalent.

The trial has been designed to determine if ketamine is superior to morphine as a prehospital analgesic. The prehospital phase ends once the patient arrives at hospital.

Randomisation will occur when the trial drug-pack is opened. The trial drug pack includes three ampoules of trial drug containing either ketamine of morphine. The ampoules of ketamine and morphine appear identical. The treating paramedic will not know which drug they are administering, hence the double blinding.

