### Patient recruitment and consent

The study aims to recruit 446 participants. Potential participants will be identified by the attending paramedic and if eligible will be enrolled into the trial.

Acute severe pain disrupts cognitive function and may impair mental capacity. Furthermore, patients with severe pain require urgent treatment to relieve pain for humanitarian reasons as well as to reduce the physiological stress caused by severe pain. It may therefore be impractical to obtain written informed consent prior to treatment from either the patient or a personal legal representative as to do so would delay treating the patient’s pain.

Before recruiting any patient to the trial, the paramedic will provide the patient with brief verbal information about the trial by reading predefined text from an aide memoire and advising the patient of their intention to enrol the patient into the trial. At this time, the paramedic will not be seeking informed written consent, but will provide the patient the opportunity to decline participation in the trial. Written informed consent will be obtained from the patient, or their legal representative, by research paramedics at the earliest opportunity, once the initial emergency has passed.

Ethics approval was granted on 01/09/2020 by West of Scotland REC 1.

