### Allocation sequence and randomisation

The randomisation sequence will be provided by the Programming Team at the Warwick CTU. Randomisation will be achieved by way of specially prepared, sequentially numbered treatment packs containing identical ampoules of either ketamine (intervention) or morphine (comparator). The content of the drug packs will be determined from a randomisation list prepared by the study programmer. The blinded block randomisation system will look to ensure a ratio of 1:1 control: intervention. The balance between arms at each site is handled by the ordering system that ensures a pre specified number of paired packs are delivered to each site. The block size is determined by the number of drugs in any given site batch order. Distribution of trial drug packs by the trial drug manufacturer will ensure equal proportions of ketamine (intervention) and morphine (comparator) are distributed to each participating site. Allocation will be concealed from study personnel, ambulance staff and patients.

Numbered study drug packs in a pre-randomised sequence, will be carried by participating ambulance paramedics. Randomisation will be achieved by opening the pack. This avoids the need for any randomisation procedures before recruitment which could delay patient treatment.

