Time to Meaningful Analgesia	Defined as a 44% change in NRS pain score from initial pain score. The time will be taken as time of meaningful analgesia minus time of first administration	If 44% change not achieved, we will score this as meaningful analgesia not achieved
Time to Peak Analgesia	Measured as the time when lowest NRS pain score, relative to initial pain score, is achieved minus time of first administration	
Duration of Analgesia	Measured as the time period in which patient pain scores have consecutively decreased or remained stationary (There may be different instances of this per patient)	
Requirement for Rescue Analgesia	We will record whether a patient has needed rescue analgesia and which analgesia was administered, Entonox, paracetamol, ibuprofen, or other	
Proportion of patients with pain intensity score below 4/10 on NRS scale	At hospital arrival the research paramedic will record a NRS pain score. We will provide the proportion, as a percentage, of each patient that achieved a score < 4/10	If there is no hospital arrival score, we will use the scores recorded in the ambulance journey
Vital Signs	At each observation time, the respiratory rate (bpm), oxygen saturations (%), heart rate (bpm), blood pressure (mmHg) and their Glasgow Coma Scale (GCS)	
Glasgow Coma Scale	Three subscales measuring eyes, verbal, and motor response of each patient. The scales are as such: Eyes 1–4 Verbal 1–5 Motor 1–6	
Global Impression of Change	Using a 7-point Likert scale. The options offered ranging from ‘very much improved’ to ‘very much worse’	
Side effects and adverse events	Measured in the following categories, ‘Airway’, ‘Respiratory’, ‘Cardiovascular’, ‘Neurologic’, and ‘other’	
Ambulance job cycle time	Time taken from arrival on scene to hospital arrival	
Number of ambulance resources	Number of doctors, paramedics, doctors, and vehicles attending scene	
Cumulative IMP doses administered	Total dose of IMP administered	
CT scan use	If patient had a CT scan and how many	
Hospital or ICU admission	Yes; no option if patient is admitted to hospital or ICU	
Length of stay in ED, ICU, or hospital	Classed as date and time of admission to date and time of discharge	
BPI-SF at 3 and 6 Months		

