### Secondary outcomes

*Effectiveness of pain relief and overall patient experience from randomisation to arrival at hospital*
Total Pain Relief (TOTPAR) scoreTime to perceptible analgesiaTime to meaningful analgesiaTime to peak analgesiaDuration of analgesiaRequirement for rescue analgesiaProportion of patients with a pain intensity score below 4/10 (0–10 numerical rating scale (NRS)) on arrival at hospitalVital signs (oxygen saturation, blood pressure, heart rate, respiration rate, Glasgow Coma Scale)Patient Global Impression of Change on arrival at hospital

*Incidence of side effects and adverse events*
Airway: vomiting, aspiration, advanced airway managementRespiratory: desaturation, need for ventilatory supportCardiovascular: arrhythmia, hypotension and hypertensionNeurologic: sedation, excitatory movements, adverse behavioural reactionsOther: nausea, allergic reaction

*Resource use*
Ambulance job cycle time (scene arrival to arrival at hospital)Number of ambulance resources (technicians, paramedics, doctors and vehicles) in attendanceCumulative IMP doses administeredCT scan useHospital or ICU admissionLength of stay ED, ICU, Hospital

*Longer term outcomes*
Chronic pain using Brief pain inventory-short form (BPI-SF) at 3 & 6 months from randomisationHealth-related quality of life measured using the EQ-5D-5L at 3 and 6 months from randomisationCost-effectiveness expressed in terms of incremental cost per quality-adjusted life year (QALY) gained

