### Sample size

In line with IMMPACT recommendations, our primary outcome reports Sum of Pain Intensity Difference (SPID). Reductions in pain severity can be reported as either change in NRS, the pain intensity difference (PID), or as a percentage change PID (%PID). The International Association for the Study of Pain has quantified clinically meaningful improvements in pain intensity. Depending on how severe the initial pain is, clinically important improvements in PID range from 1.3 to 5.2. Those with severe pain will need to experience a greater reduction in pain than those with mild pain to experience a clinically important reduction in pain. Similarly, improvements in %PID range from 20.1 to 56.1% depending on severity of pain. Previous studies have established that improvement in PID is equivalent to improvement in SPID [39].

The study has been powered to identify change in SPID calculated using the change in PID. To ensure our study is able to detect at least a 20% improvement in %SPID, regardless of baseline pain intensity, our sample size calculation is powered to detect 20% improvement in %PID, which in turn is equivalent to a 1 point difference (0–10 NRS) in effectiveness between morphine and ketamine.

Previous randomised controlled trials comparing ketamine and morphine have adopted a standard deviation of 3.0 [35, 36, 40, 41]. A review of existing prehospital studies identified that the average non-response/withdrawal rate was 14% [40, 42–45]. We therefore calculate our sample size assuming a standard deviation of 3.0, 1:1 randomisation, a power of 90%, significance level of 5% and a withdrawal/non-response rate of 15%.

Based on these estimates we calculate our trial will require a sample of 446 subjects, recruiting 223 to each arm of the study, to detect a 1 point difference on the NRS (range 0–10) in primary outcome between morphine and ketamine.

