### Data analysis

The statistical analysis will follow the estimand framework [46]. Primary analysis will be by intention to treat. The primary outcome will be the SPID, a measure of the area under the curve of the pain score difference from baseline over time. The primary outcome will be analysed using a linear regression. Both unadjusted and adjusted (for important covariates) estimates and 95% confidence intervals for the treatment effect will be obtained. The adjusted estimates will form the basis for the primary analysis. Descriptive summaries of the outcomes will be presented as frequencies or means and medians. For the adjusted estimates, the covariates used will be age (< 60; ≥ 60 years), gender, weight and alternative parenteral IV paracetamol prior to randomisation (as a dichotomy split by yes or no). Age and gender have been chosen as covariates as these groups can experience pain differently, administration of IV paracetamol prior to randomisation is included as a covariate as it is an adjunctive treatment that may impact pain response. Weight is included as a covariate since different weight groups have different requirement for an adequate dose of IMP. For continuous secondary outcomes, analysis will be carried out in a similar way to the primary outcome. For categorical outcomes, logistic regression models will be used. Participant vital signs are recorded in a longitudinal format, for these outcomes we will use a mixed effect model.

Various intercurrent events have been identified for this trial, in line with the estimand framework [46], and approaches to dealing with these have been considered. For discontinuation of the allocated treatment and use of rescue analgesia, we will follow the treatment policy, where the data is analysed as observed. Compliance with administration of the trial drug as per the trial protocol will be monitored. If there is a noticeable degree of non-compliance, we will carry out a complier average casual effects (CACE) analysis [47, 48]. If sufficient data permits, sensitivity analysis will be conducted on a modified intention to treat population, excluding participants that were randomised but the drug was not given. Again, if sufficient data permits, participant deaths will be analysed using Pocock’s win ratio method, this allows death to be interpreted as a participant outcome and infer if the intervention is significantly better than the standard care having considered the clinical priority.

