### Health economic evaluation

A health economic evaluation has been embedded into the PACKMaN trial. The economic evaluation will take the form of a within-trial cost-effectiveness analysis, conducted from the perspective of the UK NHS and personal social services [49]. Estimates of economic costs will capture resource use associated with the pre-hospital emergency response and broader utilisation of hospital and community-based health and social care services. Resource use in the pre-hospital stage will be extracted from trial case report forms completed by research paramedics. This will include the number of paramedic staff, technicians, doctors, and ambulance staff attending the patient, in addition to transport vehicle, duration of emergency response and cumulative morphine or ketamine doses administered, and medication for treatment of adverse events. Additionally, index admission hospitalisation data resource use will be extracted, this includes length of stay, and number of days receiving critical care and associated critical care level. Resource use questions completed by participants at each assessment point during the study follow-up will provide a profile of all other hospital inpatient and outpatient services, community health and social care encounters, prescribed medications, NHS supplies, time off work and out of pocket medical expenses. Health-related quality of life will be measured using the EQ-5D-5L at three and six months after randomisation. For ethical, logistical, and pragmatic reasons, it is not possible to capture baseline EQ-5D-5L measurements in patients suffering acute pain following trauma within this trial. This is not uncommon within trials in emergency and critical care settings [50]. The baseline analysis for the health economic evaluation will use a fixed baseline approach for EQ-5D-5L health utilities for all participants. This fixed value will be derived by mapping the ‘typical’ acute pain trauma case to the EQ-5D-5L using expert opinion. The sensitivity of this assumption will be tested within sensitivity analyses. Sensitivity analyses will include assigning different values to patients according to severity as determined by registration to the Trauma Audit and Research Network (TARN). TARN can be used as a proxy for severity as the most serious trauma patients will be registered onto TARN whilst less severe cases will not (non-TARN). We will then use expert opinion to estimate a baseline EQ-5D profile for both TARN and non-TARN patients. We will estimate QALY profiles for each participant over a six-month time horizon using the baseline-adjusted area-under-the curve method. We will fit a bivariate regression of costs and QALYs, with multiple imputation of missing data. We will estimate the incremental cost per QALY gained for the comparator interventions from incremental costs and incremental QALYs generated from the regressions. Cost-effectiveness estimates will also be generated for subgroups as specified in the health economics analysis plan.

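### Ambulance job cycle time includes on-scene time before randomisation, which the stated covariates do not target; adjusting for it is a minor, free gain in precision

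*Protocol article*

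**What the plan says.** The outcome is defined in two places in the protocol article, and they agree. Table 3 (Outcomes) has "Time taken from arrival on scene to hospital arrival". The list under Secondary outcomes, in the Resource use group, has "Ambulance job cycle time (scene arrival to arrival at hospital".

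On the moment of randomisation, Trial design and setting says: "Randomisation will occur when the trial drug-pack is opened". Several steps come first. The eligibility criteria require a pain score, intravenous or intraosseous access, and the paramedic's judgement of need. Patient recruitment and consent adds: "Before recruiting any patient to the trial, the paramedic will provide the patient with brief verbal information about the trial". On concealment, Allocation sequence and randomisation says: "Allocation will be concealed from study personnel, ambulance staff and patients".

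On analysis, the Data analysis section says: "For continuous secondary outcomes, analysis will be carried out in a similar way to the primary outcome". For the primary outcome that is a linear regression adjusted for age (below 60, or 60 and over), gender, weight and IV paracetamol before randomisation.

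Time also enters the costing. The Health economic evaluation lists pre-hospital items "in addition to transport vehicle, duration of emergency response and cumulative morphine or ketamine doses administered".

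**The concern.** Job cycle time is the sum of two parts: scene arrival to pack opening, and pack opening to hospital arrival. Only the second can respond to the drug. The Dosing regime gives a plausible route there: the first syringe is titrated over five minutes, pain is reassessed five minutes later, and further aliquots follow at five-minute intervals. If one drug needs more titration, the difference appears after the pack is opened.

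The first part is a pre-randomisation quantity and an arithmetic component of the outcome. No covariate in the stated model represents it, except so far as the listed ones happen to predict it. Its spread therefore goes into the residual variance. At stake is the precision with which the trial can say whether one drug ties up ambulances for longer, a question it lists among its secondary outcomes.

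**Working it through.** **The plan's own figure.** The article gives no precision or power figure for job cycle time. Its one calculation is for the primary outcome: "We therefore calculate our sample size assuming a standard deviation of 3.0, 1:1 randomisation, a power of 90" per cent, with a difference of 1 point, 5% significance (taken as two-sided) and 15% loss. Per arm, n = 2 × [3.0 × (1.960 + 1.282)]² / 1² = 189.13. Dividing by 0.85 gives 222.5, rounded up to 223, or 446 in total. The figure reproduces, and nothing below changes it.

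**Bias.** Concealed randomisation balances time before pack opening in expectation, so the expected arm difference in minutes is the same whether the clock starts at scene arrival or at pack opening. An illustrative simulation bears this out (190 per arm, true difference −3 min, independent intervals with assumed distributions). The mean estimate was −2.98 min under both definitions. The empirical standard error was 2.04 min from scene arrival and 1.76 min from pack opening.

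**Variance.** Let r be the SD of the time before pack opening divided by the SD of the time after it, and ρ their correlation. In units of the post-pack variance:

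- full cycle time, no covariate for pre-pack time: 1 + r² + 2ρr
- pack opening to hospital arrival alone: 1
- full cycle time, adjusted linearly for pre-pack time: 1 − ρ²

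The gain from adjustment is (1 + r² + 2ρr) − (1 − ρ²) = (r + ρ)², which is never negative. The adjusted analysis is also at least as precise as the post-pack interval alone, because 1 − ρ² ≤ 1.

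**Illustrative range.** The article gives neither r nor ρ, so the values below are assumptions. Cells show variance, with power in brackets, for a difference that would have 90% power on the post-pack interval alone with 190 per arm. Power is Φ[(1.960 + 1.282)/√variance − 1.960].

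| ρ | With covariate | No covariate, r = 0.25 | r = 0.5 | r = 0.75 | r = 1 |
|---|---|---|---|---|---|
| +0.3 | 0.910 (92%) | 1.213 (84%) | 1.550 (74%) | 2.013 (63%) | 2.600 (52%) |
| 0 | 1.000 (90%) | 1.063 (88%) | 1.250 (83%) | 1.563 (74%) | 2.000 (63%) |
| −0.3 | 0.910 (92%) | 0.913 (92%) | 0.950 (91%) | 1.113 (87%) | 1.400 (78%) |
| −0.5 | 0.750 (96%) | 0.813 (95%) | 0.750 (96%) | 0.813 (95%) | 1.000 (90%) |

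The gain runs from nothing (r = 0.5, ρ = −0.5) to large (r = 1, ρ = +0.3). Some cells without the covariate have a variance below 1. There, moving the start of the clock to pack opening would lose precision, while adding the covariate would not. All values are before the existing covariates. If those partly predict pre-pack time, as prior IV paracetamol might, the gain changes accordingly.

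**The case against.** The strongest reply is that nothing here is wrong. The two definitions agree, and the outcome sits under Resource use, apart from the efficacy outcomes that run from randomisation. The ambulance is committed from scene arrival, and the duration of the response is costed. A reader might infer that the time before pack opening is mere noise and should be cut from the outcome. The documents do not support that: those minutes belong to the quantity measured, and moving the clock could lose precision if the two parts are negatively correlated.

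A reader might also infer bias, or a separate harm from chance imbalance. Neither follows. The expected difference is unchanged, and chance imbalance is already reflected in the standard error.

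A third tempting reading is a definite loss. With an assumed SD of 25 min after pack opening, 10 to 25 min before it, and no correlation, the variance would rise by 16% to 100%. Every input there is assumed, so it is not an estimate for this trial.

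It is also fair to say that one covariate for an unpowered secondary outcome is the kind of detail an analysis plan settles, and that plan is not shown. This limits the weight of the point. It does not remove it, because the article names the covariate set and extends the primary approach to continuous secondary outcomes.

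Finally, the article does not say that pack opening is timestamped. First administration is the stated anchor for the time-to-analgesia outcomes. That objection stands and is met in the fix.

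**Conclusion.** The point holds as a minor, free improvement, not as an error in the plan. The outcome is consistently defined, suits its purpose and gives an unbiased comparison. The comparison carries variance that allocation cannot affect and that no stated covariate represents. The direction of the benefit from adjustment does not depend on assumed values: the variance falls by (r + ρ)² in units of post-pack variance, before one degree of freedom is spent. Its size cannot be estimated from the article and could be close to zero. The conclusion rests on concealed allocation, on pack opening following the on-scene steps, and on a linear adjustment. The primary outcome, the sample size of 446 and the costing input are unaffected.

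**What to change.** Keep job cycle time as defined, for the arm comparison, for description and for costing. In the between-arm model for this outcome, add the interval from scene arrival to pack opening as a continuous covariate beside those already named.

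The sponsor should confirm whether pack opening is timestamped. If it is not, use scene arrival to first administration. This ends shortly after randomisation, but identical ampoules and blinding keep it independent of arm. In that case, state how participants who were randomised but not given drug are handled, since they have no administration time and the Data analysis section anticipates such a group.

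Optionally, report pack opening to hospital arrival as a supplementary interval. It still contains the journey, so it should not be labelled on-scene time.

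The cost is one sentence in the analysis plan and one degree of freedom. With the fallback, no new data should be needed: scene arrival is required for this outcome and first administration for the time-to-analgesia outcomes.

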## Outcomes

Table 2 presents the timings of when study outcome measures will be collected. Table 3 details the definition and methods to calculate the study outcomes.

**Table 2 Tab2:** Schedule of delivery of intervention and data collection

Visit	1	2	3	4
Visit Window (No. Weeks ± No. Days)	Baseline/Pre hospital/Hospital arrival	After hospital arrival	3 m (± 2w)	6 m (± 1 m)
Trial Information	✓	✓		
Informed consent		✓		
Randomisation	✓			
Vital signs	✓			
Inclusion/exclusion criteria	✓			
Intervention	✓			
Rescue analgesia	✓			
Quality of Life—EQ-5D-5L			✓	✓
Side effects & Adverse events	✓	✓	✓	✓
Questionnaire—BPI-SF			✓	✓
Questionnaire—CSRI			✓	✓
SPID	✓			
TOTPAR	✓			
Time to perceptible analgesia	✓			
Time to meaningful analgesia	✓			
Time to peak analgesia	✓			
Duration of analgesia	✓			
Patient Global Impression of Change	✓			
Resource use	✓	✓	✓	✓

**Table 3 Tab3:** Outcome measure definitions

	Definition	Mitigations
*Primary outcome*		
Effectiveness of pain relief from randomisation to arrival at hospital as measured by Sum of Pain Intensity Difference (SPID) score (using a 0–10 numerical rating scale)	The SPID is measured using a weighted sum of the scores, as shown below: $$SPID_{n} = \mathop \sum \limits_{i - 1}^{n} \left( {T_{i} - T_{i - 1} } \right)*PID_{i}$$ *T*_*i*_ is the time in hours when observation *i* is taken *PID*_*i*_ is the difference in Pain Intensity (PI) scores from initial pain score to the pain score at time *T*_*i*_. The SPID looks to calculate the area under the curve of pain intensity different over time	
*Secondary outcomes*		
The Total Pain Relief (TOTPAR)	The TOTPAR is measured using a weighted sum of the scores, as shown below: $${TOTPAR}_{n}= \sum_{i-1}^{n}\left({T}_{i}-{T}_{i-1}\right)*{PAR}_{i}$$ *T*_*i*_ is the time in hours when observation *i* is taken *PAR*_*i*_ is the pain relief score measured as defined below on a scale of 1 to 3 We measure minimal pain relief as 1.8 (1.7–1.9) change in pain score, much pain relief as 4.0 (3.9–4.1) and very much pain relief as 5.2 (5–5.4) Percentage changes defined as 20.3 (19–21.6), 44.4 (43.2–45.6), 56.1 (53.9–58.4) respectively	
Time to Perceptible Analgesia	Perceptible pain relief is defined as a 20% change in NRS pain score from the initial pain score. The time will be taken as time of perceptible analgesia minus time of first administration	If 20% change not achieved, we will score this as perceptible analgesia not achieved

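### Hospital and ICU stay have no value for a patient never admitted, so taken literally the plan compares only admitted patients, and the comparison can point the wrong way

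*Protocol article*

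**What the plan says.** Table 3 in the Outcomes section of the protocol article is introduced as the place where outcome definitions and calculation methods are given. Its row for length of stay covers ED, ICU and hospital together and reads "Classed as date and time of admission to date and time of discharge". The Mitigations cell for that row is empty.

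The row just above makes admission an outcome in its own right: "Yes; no option if patient is admitted to hospital or ICU". The list of secondary outcomes places both under resource use.

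The Data analysis section adds "For continuous secondary outcomes, analysis will be carried out in a similar way to the primary outcome". The model for the primary outcome is a linear regression, unadjusted and adjusted. The same section says "Primary analysis will be by intention to treat".

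For comparison, the row for time to perceptible analgesia does cover the patient in whom the event never happens: "If 20% change not achieved, we will score this as perceptible analgesia not achieved".

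**The concern.** The yes/no admission outcome shows that the trial expects some patients not to be admitted. For them, the admission-to-discharge definition returns nothing for hospital stay. The same applies to ICU stay for anyone who never enters ICU. ED stay is much less affected, because patients taken to an ED would have one.

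A linear regression uses only patients with an outcome value. If nothing is assigned to the others, the regression compares admitted patients in one arm with admitted patients in the other. Admission happens after randomisation and could differ by arm, for example through sedation, vomiting or pain control on arrival. The two admitted groups then need not be comparable.

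The error also has a likely direction. If a treatment prevents some admissions, the prevented ones are plausibly the short ones. Removing short stays raises the mean of those left, so the arm that uses fewer beds appears to have longer stays.

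**Working it through.** **The plan's own figure.** The article gives no number for length of stay. Its one relevant figure is 223 per arm, used below as the denominator. From the Sample size section (SD 3.0, difference 1 point, power 90%, 5% significance taken as two-sided, 15% loss):

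- n per arm = 2 × (1.960 + 1.282)² × 3² / 1² = 189.13
- 189.13 / 0.85 = 222.5, rounded up to 223 per arm, 446 in total.

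The stated size reproduces. (Rounding to 190 before inflating gives 224 per arm, 448 in total.) Nothing below changes it.

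**General form.** Suppose *a* patients per arm would be admitted, with mean stay *m*, and one arm avoids *k* admissions of length *s*, with *N* randomised per arm.

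- Change in mean among admitted = k(m − s)/(a − k)
- Change in mean over all randomised, non-admitted = 0: −ks/N

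The second is always a reduction. The first is an increase whenever s < m, that is, whenever the avoided stays are shorter than average. If the avoided stays are longer than average, the two agree in sign.

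**Illustration 1 (all inputs assumed except 223 per arm).** Morphine: 80 not admitted, 40 stay 1 day, 103 stay 5 days. Ketamine: the same, but 20 of the 1-day admissions are avoided.

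- Bed-days: morphine 40 × 1 + 103 × 5 = 555; ketamine 20 × 1 + 103 × 5 = 535.
- Among admitted: 555/143 = 3.88 vs 535/123 = 4.35 days. Ketamine looks 0.47 days longer.
- Over all randomised: 555/223 = 2.49 vs 535/223 = 2.40 days. Ketamine is 0.09 days shorter.

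**Illustration 2 (range, all inputs assumed).** In the control arm 40% of stays last 1 day and 60% last 8 days, so the mean among admitted is 0.4 × 1 + 0.6 × 8 = 5.20 days. The intervention avoids 1-day admissions in 5% or 10% of all patients.

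| Admitted, control | Avoided | Mean among admitted, control vs intervention | Difference | Mean over all randomised, control vs intervention | Difference |
|---|---|---|---|---|---|
| 30% | 5% | 5.20 vs 6.04 | +0.84 | 1.56 vs 1.51 | −0.05 |
| 30% | 10% | 5.20 vs 7.30 | +2.10 | 1.56 vs 1.46 | −0.10 |
| 50% | 5% | 5.20 vs 5.67 | +0.47 | 2.60 vs 2.55 | −0.05 |
| 50% | 10% | 5.20 vs 6.25 | +1.05 | 2.60 vs 2.50 | −0.10 |
| 70% | 5% | 5.20 vs 5.52 | +0.32 | 3.64 vs 3.59 | −0.05 |
| 70% | 10% | 5.20 vs 5.90 | +0.70 | 3.64 vs 3.54 | −0.10 |

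For example, row 1: (0.07 × 1 + 0.18 × 8)/0.25 = 6.04.

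The sign reverses in every row. That follows from the assumption that only 1-day stays are avoided; it is not evidence about this trial.

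**The case against.** A reader might infer that the plan excludes non-admitted patients and so abandons intention to treat for this outcome. The text does not say that. Table 3 says how a stay is measured, not who is analysed, and counting 0 for a patient never admitted is compatible with it. The article refers to a separate detailed analysis plan, which may contain such a rule. Many other Table 3 rows also have an empty Mitigations cell, so an empty cell is no decision to exclude. This objection stands against any claim that exclusion is planned. It does not remove the point: the article states a calculation that cannot be applied to some randomised patients and names the model that would then omit them. It states intention to treat in terms of the primary analysis, without saying what value a non-admitted patient takes.

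The article also limits the possible misreading. Admission is reported separately, so a shift in admissions would be visible. Bed use enters the economic evaluation, where "index admission hospitalisation data resource use will be extracted, this includes length of stay". Both help a careful reader, but neither corrects a stay estimate that has the wrong sign.

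A reader might also object that an early death in hospital scores as a short stay and so looks like a good result. As length of stay is listed as resource use, a short stay is then an accurate record of beds used. The article plans a separate win-ratio analysis of deaths if data permit. This gives no reason to penalise deaths within the stay outcome.

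Finally, the illustrations are constructed, and the documents contain nothing with which to calibrate them. That is correct.

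**Conclusion.** The point holds in conditional form. Table 3 leaves hospital and ICU stay undefined for patients not admitted. Combined with linear regression, the plan taken literally compares a subset selected after randomisation. If one arm avoids admissions shorter than average, that comparison shows the arm as worse when it used fewer bed-days.

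The documents do not establish that this analysis will be done, nor that admission will differ between arms. With no admission rate or stay distribution given, the size is unknown. Under the assumed inputs, the apparent excess among admitted patients is 0.3 to 2.1 days, while the difference over all randomised patients is 0.05 to 0.10 days in the other direction. These figures show the mechanism only.

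The consequence is confined to a secondary resource-use outcome. It is worth correcting because the correction is nearly free, not because it threatens the trial's main conclusion.

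**What to change.** Amend the length-of-stay row in Table 3 and align the analysis plan:

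- Compare hospital stay and ICU stay between arms over all randomised patients, with 0 for a patient known not to have been admitted to hospital or to ICU respectively. Unknown admission status remains missing and is not set to 0.
- Keep the planned regression for the mean difference, but use an interval robust to many zeros and to skew, such as a bootstrap interval.
- Show stay among admitted patients by arm as description only, beside the proportion admitted and the number of in-hospital deaths.

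Deaths need no special score and the outcome need not be replaced, because it measures resource use.

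The cost is wording. Admission status and admission and discharge times are already collected under Table 3. The downside is that a mean over all patients is less familiar to hospitals than stay per admission, which is still reported. If the analysis plan already sets non-admitted patients to 0, only Table 3 needs to be aligned.
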